**Fig. 2 Fig2:**
[figure not shown]
Illustrative example of the interrupted time series approach with estimated coefficients; $${\beta }_{0}$$ the trend prior to the intervention, $${\beta }_{1}$$ the immediate (local) effect following the intervention; $${\beta }_{2}$$ the post-intervention trend (target population measure)

#### Secondary hypotheses

We will also test multiple secondary hypotheses to assess the additional impact of the implementation strategy. These include: (1) the rate of SSI does not change post-intervention and (2) the rate of CDI decreases post-intervention. Analogous ITS-type statistical models will be fitted to investigate secondary outcomes. All estimated effects will be reported as odds ratios with 95% confidence intervals and p-values. The tests will be two-sided with a 5% statistical significance level and will be conducted using R statistical software.

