**Discussion:**

By scaling up this intervention, the study aims to provide a robust evaluation of its effectiveness across diverse hospital settings. If successful, this approach could inform future antimicrobial stewardship efforts in pediatric and adult surgical populations, offering a scalable model for reducing inappropriate antibiotic use while maintaining patient safety.

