#### Power and sample size calculations

The sample size calculation is based on the primary outcome of the percentage of cases in which unnecessary postoperative antibiotic prophylaxis is administered among clean and clean-contaminated cases in the 20 participating hospitals. For the purposes of the power calculation, the staggered temporal implementation of the intervention in each of the hospitals is approximated by assuming a stepped-wedge cluster randomized trial design and adopting the sample size formula and associated web-based tool of Hemming and colleagues [35]. Utilizing data from our previous clinical trial specific to spine procedures [36], this sample size calculation depends on the targeted effect size (a percentage decrease from 45% measured in the pre-intervention period), the number of steps (10, with two hospitals implementing the intervention approximately every month over a period of 12 months), the estimated number of procedures per month (14 per hospital per month), and the intra-cluster correlation (ICC) coefficient (estimated at 0.12 from previous studies) [37]. With 20 hospitals implementing the intervention over a (1 [pre-] + 1 year [training] + 3 [post] =) 5 year study period, we envisage attaining at least 80% power to detect a difference in the pre- and post-intervention outcome measure of at least 5%, with a (two-sided) statistical significance level of 5% (and no missing data). Here we assume that existing surveillance measures capture data for the pre-intervention period and make the conservative assumption that all participating hospitals have one or more years pre-intervention surveillance data (not part of the study period), and *at least* 3 years post-intervention follow-up, allowing for the 12-month lag in post-training effect.

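### The hypothesis of an unchanged SSI rate is paired with a two-sided test of difference and no margin, so the planned test cannot support it

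*Protocol article*

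**What the plan says.** Under Secondary hypotheses, the first hypothesis to be tested is "1) the rate of SSI does not change post-intervention"; the second is a fall in CDI. One method serves both: "Analogous ITS-type statistical models will be fitted to investigate secondary outcomes". The section adds "All estimated effects will be reported as odds ratios with 95% confidence intervals and p-values" and "The tests will be two-sided with a 5% statistical significance level".

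No non-inferiority or equivalence margin appears anywhere in the article, nor any limit on an acceptable rise in SSI or any rule for reading the SSI interval. Power and sample size calculations covers the antibiotic outcome only: "The sample size calculation is based on the primary outcome of the percentage of cases in which unnecessary postoperative antibiotic prophylaxis is administered". The Discussion part of the Abstract hopes for a model "reducing inappropriate antibiotic use while maintaining patient safety".

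**The concern.** The two secondary hypotheses make opposite kinds of claim. A fall in CDI is a difference, and a two-sided test of difference suits it. An unchanged SSI rate is the null of that same test. Failing to reject a null is not evidence for it, and failure becomes more likely as the data become less precise. With no margin, nothing in the stated method could count in favour of the SSI hypothesis except non-significance.

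SSI is the harm to be weighed against giving less prophylaxis. The Background names surgeons' wish to balance SSI risk against antibiotic excess as a barrier, and the Discussion foresees extension to other pediatric and adult settings. A claim that safety was maintained would lean heavily on this one analysis.

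**Working it through.** **Plan's own figure.** There is none for SSI: no baseline rate, power or margin is stated. The question is how large a rise could stay unexcluded when the result looks null.

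**Inputs from the article**
- 20 hospitals and 14 procedures per hospital per month (Power and sample size calculations; based on spine procedures).
- Up to 1,500 cases annually at each hospital (Clinical data; all wound classes, so a ceiling).
- Three years before and three after (Data collection), taken as 36 months each.
- ITS model with level and slope terms, with differences also examined at 12, 24 and 36 months (Primary hypothesis).

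**Assumptions.** SSI rate p of 1%, 2% or 3%. Staggered starts and the hospital random intercept are ignored.

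**Volumes**
- Planning: 20 × 14 = 280 per month; 280 × 36 = 10,080 per period.
- Ceiling: 20 × 1,500 / 12 = 2,500 per month; 2,500 × 36 = 90,000 per period.

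**Simple pre/post odds ratio.** SE = √(2 / (n p(1−p))). At n = 10,080 and p = 1%, SE = √(2/99.8) = 0.142. With an estimate of OR 1 the upper limit is exp(1.96 × 0.142) = 1.32; at 2% and 3% it is 1.22 and 1.18. An estimate just short of significance has upper limit exp(2 × 1.96 × SE) = 1.74, 1.48 and 1.38.

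**ITS contrast 24 months after the interruption.** This is the post-period line minus the pre-period line projected forward. Let w be the monthly information, (cases per month) × p(1−p). Each 36-month segment has mean month 17.5 and sum of squares 36 × (36² − 1)/12 = 3,885.
- Post line at month 24: 1/36 + (24 − 17.5)²/3,885 = 0.0387.
- Pre line projected to month 60: 1/36 + (60 − 17.5)²/3,885 = 0.4927.
- Variance = 0.5314 / w. The simple comparison has (2/36)/w = 0.0556/w, so the inflation is about 9.56. For the immediate level change the same method gives 4.0.

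At the planning volume and p = 1%, w = 280 × 0.0099 = 2.772, SE = √(0.5314/2.772) = 0.438, and the upper limit is exp(1.96 × 0.438) = 2.36.

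| 24-month ITS contrast | SSI 1% | SSI 2% | SSI 3% |
|---|---|---|---|
| Upper limit at estimated OR 1, 14 per hospital per month | 2.36 | 1.84 | 1.65 |
| Power for a true OR of 1.5, same volume | 15% | 26% | 36% |
| Upper limit at estimated OR 1, 1,500 per hospital per year | 1.33 | 1.23 | 1.18 |

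If the 12-month lag splits the 72 months into 48 and 24, the planning-volume limits become 2.21, 1.76 and 1.59. The picture is the same.

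**Feasibility of a margin (illustrative margins only).** For a simple comparison with equal true rates, one-sided 2.5% and 80% power, n per period = (1.96 + 0.84)² × 2p(1−p)/δ².
- δ of 1 percentage point: 1,555, 3,077 and 4,569 cases at 1%, 2% and 3%.
- δ of 0.5 point: 6,217, 12,308 and 18,273 cases.

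Multiplying by 9.56 gives a rough size for the 24-month ITS contrast. For the 1-point margin that is about 14,900 (1,555 × 9.56) to 43,700 (4,569 × 9.56), above the planning volume but below the ceiling. For 0.5 point at 2% it is about 117,700 (12,308 × 9.56), above both.

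**The case against.** The strongest reply is that the article states no decision rule for SSI. A reader might infer that a non-significant p-value will be announced as proof of safety, but the text does not say so. Study design speaks only of investigating change in SSI and CDI, which fits two-sided estimation, and the phrase about patient safety in the Abstract is a conditional hope. Confidence intervals are also promised, so any unexcluded rise will be visible. All of this stands, and it narrows the point to a hypothesis the stated test cannot support, with no pre-set criterion for the interval.

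The volume can also be challenged. The 14 per month is a spine-specific planning figure for another outcome, whereas the clinical models use the whole NSQIP-P analysis set, and 20 hospitals is a minimum. This stands too, which is why the ceiling is shown. A reader might infer from the planning figures alone that a near-doubling of SSI would go unexcluded; at the ceiling that is not so. The ceiling covers all wound classes, so with 20 hospitals the relevant volume for clean and clean-contaminated cases should be lower than that.

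Finally, a full analysis plan might contain a margin. It may, but the article already fixes the hypothesis, model, sidedness and level. A margin-based analysis would change that stated rule, not fill in a detail left open.

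**Conclusion.** The point holds in this limited form. The article sets out to test that SSI is unchanged and prescribes a method that can only contradict that hypothesis. It gives no margin for reading the interval it will report. It does not commit the authors to treating non-significance as safety, and that should not be attributed to them.

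The size depends on an SSI rate and a case volume the article does not give. For assumed rates of 1% to 3%, a 24-month contrast estimated at exactly no effect leaves a rise of 65% to 136% in the odds unexcluded at the planning volume, and 18% to 33% at the ceiling. Staggered starts and random effects are not included. More cases shrink the interval but do not make a test of difference support no change.

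SSI is a secondary endpoint, and the primary analysis and its sample size are unaffected. This should be fixed, but it does not threaten the study's main result.

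**What to change.** In Secondary hypotheses, restate SSI as a non-inferiority hypothesis on one named post-versus-pre contrast from the planned ITS model. Agree a clinically justified margin, on the odds ratio or absolute scale, before post-intervention SSI data are examined. Conclude that a material rise is excluded only if the upper limit of the two-sided 95% confidence interval lies below the margin; otherwise report the result as inconclusive. Keep the two-sided test for CDI.

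If no margin can be agreed, the minimum is one sentence stating that SSI will be estimated with its 95% confidence interval and that a non-significant result will not be taken as evidence of no change.

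The cost is one paragraph and agreement on a margin, with no new data. Because NSQIP-P data are to be requested shortly after the workshop and then annually, the margin should be settled early. The downside is that the SSI conclusion may be inconclusive, especially at later ITS time points.

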#### Missing data

Based on our previous studies, since we do not foresee a large percentage of either endpoint or covariate missingness in the data, the primary analysis will consider the complete case data only. If the level of missingness exceeds 5% for any specific covariate of interest, then multiple imputation under the missing at random (MAR) assumption will be performed [33]. The estimates from the fitted models with these full data sets will be compared with those from the complete case analysis, and any discrepancies will be discussed in subsequent scientific publications. Furthermore, following these analyses if the MAR assumption is deemed questionable, then appropriate sensitivity analyses will be performed to investigate plausible departures from this assumption [34].

#### Power and sample size calculations

The sample size calculation is based on the primary outcome of the percentage of cases in which unnecessary postoperative antibiotic prophylaxis is administered among clean and clean-contaminated cases in the 20 participating hospitals. For the purposes of the power calculation, the staggered temporal implementation of the intervention in each of the hospitals is approximated by assuming a stepped-wedge cluster randomized trial design and adopting the sample size formula and associated web-based tool of Hemming and colleagues [35]. Utilizing data from our previous clinical trial specific to spine procedures [36], this sample size calculation depends on the targeted effect size (a percentage decrease from 45% measured in the pre-intervention period), the number of steps (10, with two hospitals implementing the intervention approximately every month over a period of 12 months), the estimated number of procedures per month (14 per hospital per month), and the intra-cluster correlation (ICC) coefficient (estimated at 0.12 from previous studies) [37]. With 20 hospitals implementing the intervention over a (1 [pre-] + 1 year [training] + 3 [post] =) 5 year study period, we envisage attaining at least 80% power to detect a difference in the pre- and post-intervention outcome measure of at least 5%, with a (two-sided) statistical significance level of 5% (and no missing data). Here we assume that existing surveillance measures capture data for the pre-intervention period and make the conservative assumption that all participating hospitals have one or more years pre-intervention surveillance data (not part of the study period), and *at least* 3 years post-intervention follow-up, allowing for the 12-month lag in post-training effect.

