Participants will also learn techniques for presenting and visualizing evidence to effectively influence surgical colleagues and promote team-driven, sustainable practice improvements. The live webinar will be offered quarterly over a two-year period, training approximately 20 participants per session. An asynchronous version, including recorded content, complementary materials, and interactive activities, will be available through the Nationwide Children’s Hospital CME website for ongoing access. Completion of the training provides access to quarterly collaborative meetings and the opportunity to contribute to ongoing data collection as part of the broader study.

Similarly, we will provide an asynchronous version of the workshop that will include pre-recorded presentations, activities, and opportunities to engage with Operatic community who have also participated in the workshop.

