### Clinical outcomes

#### Primary hypothesis

We hypothesize that the appropriately lagged post-intervention percentage of cases receiving unnecessary postoperative antibiotic prophylaxis will be significantly lower than in the pre-intervention period. To test this hypothesis, we will use an intention-to-treat approach for the primary analysis, including all complete case patient data from the NSQIP-P analysis set. A mixed-effects logistic interrupted time series (ITS) regression model will assess the impact of "order set change resulting in reduction" (1) versus "no order set change" (0) on prophylaxis prescriptions. The model will include the intervention (pre vs. post), time (in months), and an interaction term between time and intervention, including a random intercept to account for intra-hospital correlation in the model. The post-intervention slope (β_2) will be the primary estimate of interest (Fig. 2), but we will also investigate differences at 12, 24 and 36 months. The interruption point will be 12 months after each hospital’s first training, with sensitivity analyses at lags 9, 15, and 18 months as well. We will extend the model to adjust for age, surgical subspecialty, procedure type, hospitalization duration, and co-morbidities using Akaike information criterion (AIC)-based variable selection. Subgroup analyses by procedure type and hospital will also be conducted.

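### The stated 80% power for a 5-point difference does not follow from the printed stepped-wedge inputs, which give about 60–68%, and the calculation matches neither the analysed population nor the primary estimate

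*Protocol article*

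**What the plan says.** In the protocol article, Power and sample size calculations describes the staggered roll-out as approximated by "assuming a stepped-wedge cluster randomized trial design and adopting the sample size formula" of a published web tool. The printed inputs are:

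- 20 hospitals;
- "the number of steps (10, with two hospitals implementing the intervention approximately every month over a period of 12 months");
- 14 procedures per hospital per month;
- an ICC of 0.12, attributed to previous studies;
- a baseline of 45%;
- a study period of one year before, one year of training and three years after;
- a test "with a (two-sided) statistical significance level of 5% (and no missing data").

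The conclusion is "we envisage attaining at least 80% power to detect a difference in the pre- and post-intervention outcome measure of at least 5" per cent.

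The section defines the outcome among clean and clean-contaminated cases but introduces its inputs with "Utilizing data from our previous clinical trial specific to spine procedures". Under Primary hypothesis, the analysis is a mixed-effects logistic ITS model "including all complete case patient data from the NSQIP-P analysis set". It has a pre/post term, time in months and their interaction, and the post-intervention slope (β2) is the primary estimate.

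**The concern.** There are three separate mismatches.

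1. The inputs and the result are both printed, and they disagree: the formula family that the article names does not return 80% from these inputs.
2. The data behind the inputs are for spine procedures, while the outcome is defined over every clean or clean-contaminated case. Baseline percentage, monthly volume, ICC and achievable effect may all differ between the two.
3. The quantity powered is a pre/post difference, while the quantity named as primary is a slope. Power for one says little about power for the other.

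The 80% figure is the only quantitative support given for 20 hospitals. A reader who later meets an inconclusive primary result would rely on it to judge whether the study could have found the effect.

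**Working it through.** **Inputs** (all from Power and sample size calculations): I = 20 hospitals; T = 60 months (12 + 12 + 36); two hospitals crossing over at each of ten steps; m = 14; ICC = 0.12; p₁ = 0.45, p₂ = 0.40; two-sided α = 0.05.

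**Assumptions**, because the article does not print its formula: Hussey–Hughes model, categorical months, random hospital intercept and, in the base case, cluster autocorrelation of 1.

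**Variance components.** Mean p = 0.425, so total variance = 0.425 × 0.575 = 0.2444.
- Between hospitals: τ² = 0.12 × 0.2444 = 0.02933.
- Hospital-month mean: σ² = 0.88 × 0.2444 / 14 = 0.01536.

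**Formula.** With X = 1 for an exposed hospital-month, U = ΣX, W = the sum over months of squared month totals, and V = the sum over hospitals of squared hospital totals:

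Var = Iσ²(σ² + Tτ²) / [(IU − W)σ² + (U² + ITU − TW − IV)τ²]

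The numerator is 20 × 0.01536 × (0.01536 + 60 × 0.02933) = 0.5453.

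**Attempt to reproduce the 80%.**

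*Ten consecutive monthly steps* (months 13 to 22): U = 870, W = 16,740, V = 38,010.
- Denominator = 660 × 0.01536 + 36,300 × 0.02933 = 1,074.6.
- SE = √(0.5453 / 1,074.6) = 0.0225.
- Power = Φ(0.05/0.0225 − 1.96) = Φ(0.26) = **60%**.

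*Ten steps 1.2 months apart, rounded to whole months*: U = 852, W = 16,232, V = 36,544.
- Denominator = 808 × 0.01536 + 43,504 × 0.02933 = 1,288.2.
- SE = 0.0206.
- Power = Φ(0.47) = **68%**.

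**What would give 80%.** The detectable difference is (1.96 + 0.84) × SE, which is 2.80 × 0.0206 = 5.8 points to 2.80 × 0.0225 = 6.3 points. For 5 points, the smallest monthly volume reaching 80% is 19 (12-month spread) or 23 (ten consecutive months).

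**Variants around the printed set-up:**

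| Change | Power |
|---|---|
| Cluster autocorrelation 0.9 | 53–61% |
| ICC from 0.01 to 0.20 | 56–72% |
| 36 pre-intervention months | 61–70% |
| 12-month lag, lag months counted as control | 60–68% |
| Roll-out window only (11 monthly periods) | 41% |
| 5% read as relative (45% to 42.75%) | 17–19% |

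None reaches 80%.

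**Set-ups that do exceed 80%**, each of which departs from the printed inputs or from the standard model:

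| Change | Power for 5 points |
|---|---|
| Linear secular trend, level change | 98% |
| 20 hospitals spread over eight quarterly starts | 89–90% |
| 30 procedures per month | 90–95% |
| 11 equal periods of about 5.5 months | 98% (81% at autocorrelation 0.9) |

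**The case against.** The article calls the stepped wedge an approximation and prints neither the period layout nor the time-effect model, so the 60–68% rests on a layout supplied here. That stands as a limit on certainty: a coarser layout of 11 long periods does give more than 80%. It conflicts with roughly monthly steps, however, so it does not rescue the printed calculation.

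The planned ITS model uses time in months rather than month indicators, and under a linear trend a 5-point level change has about 98% power. This also stands, but the power section does not say that it used such a model, and a level change is not the slope named as primary.

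Three stronger readings are tempting and are not supported.

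- *The study is underpowered, or needs more hospitals.* A linear trend, a longer roll-out or a larger caseload would each exceed 80% for an undiluted 5-point effect, and 20 hospitals is a minimum.
- *The roll-out assumption contradicts the training schedule.* Workshop content and delivery says "The live webinar will be offered quarterly over a two-year period", but that is when webinars are offered, alongside an asynchronous version. It does not fix when the 20 hospitals train, and a quarterly roll-out would raise power.
- *The effect will be diluted to a fraction of a point because only spine cases can improve.* The article says that stewardship teams in the earlier trial targeted different procedures and names spine only as an example. The 1,500 cases a year is a ceiling across all wound classes.

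The ICC is also attributed to previous studies, not expressly to spine.

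**Conclusion.** The concern holds as a fault in the printed justification. On the stated inputs and a standard stepped-wedge model, power for an absolute 5-point difference is about 60–68%, falling to 53–61% at a cluster autocorrelation of 0.9, against the stated minimum of 80%. This rests on categorical months and a random hospital intercept, neither of which the article confirms.

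Independently of that arithmetic, the calculation draws on spine data for an outcome defined over all clean and clean-contaminated cases, and it powers a pre/post difference where the primary estimate is a post-intervention slope. The documents do not allow power for that slope in that population to be calculated, so whether 20 hospitals are enough remains open.

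**What to change.** 1. Withdraw or restate the 80% figure. It should not simply be replaced by 60–68%, which describes the approximating design and not the planned analysis.
2. State the target difference in absolute percentage points, and state the period layout, time-effect model and within-hospital correlation structure assumed.
3. Recompute power by simulation for the primary ITS contrast, using the planned roll-out, the 12-month lag and the follow-up that will be available. Take the baseline percentage, ICC and monthly volume from existing NSQIP-P data on clean and clean-contaminated cases, and state the effect expected across that whole set.
4. Repeat the wound-class restriction under Primary hypothesis, so that the analysed and powered populations are visibly the same.

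The cost is a recalculation and possibly a less favourable stated figure. The recalculation itself needs no new data collection; whether the number of hospitals is adequate should be judged from its result.
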